#### 2.5.2. Comparator: Synthetic Vitamin D_3_

The comparator contains synthetic cholecalciferol (vitamin D_3_) sourced as a pharmacopoeia-compliant cholecalciferol concentrate powder (Vitamin D_3_ 100; product code 015209; CAS 67-97-0), compliant with the European Pharmacopoeia monograph “Cholecalciferol concentrate powder form”. The declared potency of the raw material is ≥100,000 IU vitamin D_3_/g (≥2500 μg/g), with defined physical specifications including particle size distribution (100% through 30 mesh; ≥90% through 50 mesh; ≤25% through 120 mesh) and loss on drying ≤ 5% (105 °C).

Supplier specifications include predefined limits for heavy metals (total ≤10 ppm; lead ≤ 0.5 ppm; arsenic ≤ 1 ppm; mercury ≤ 0.1 ppm; cadmium ≤ 0.5 ppm) and microbiological acceptability criteria (total aerobic count ≤ 1000 CFU/g; yeasts and molds ≤ 100 CFU/g; *Salmonella* negative/25 g; *Escherichia coli*, *Staphylococcus aureus*, and *Pseudomonas aeruginosa* negative/10 g; Enterobacteriaceae negative/g). The material includes food-/pharmaceutical-grade excipients, and vitamin D_3_ is sourced from wool grease (lanolin).

For the final comparator capsule, vitamin D_3_ is formulated in an oil-based vehicle using medium-chain TG (MCT) as carrier and alpha-tocopherol acetate as antioxidant within a hard gelatin capsule.

#### 2.5.3. Product Handling, Storage, and Accountability

Study products will be handled in accordance with label instructions and International Council for Harmonization Good Clinical Practice (ICH-GCP) principles. They will be stored in a dry, secure location at a controlled room temperature (≤25 °C), protected from excessive heat, moisture, and direct light, with access restricted to authorized study personnel only. Product integrity will be ensured through routine verification of packaging conditions and expiry dates prior to dispensing; any temperature excursions, damage, or other irregularities will be documented and managed according to site procedures.

Dispensing will be performed using treatment kits identified by study-specific codes to preserve allocation concealment and will be recorded in dedicated accountability logs, including participant identification, kit code, quantity dispensed, dispensing dates, and staff signature. The accountability documentation will allow full traceability of investigational product movement from receipt to final reconciliation.

At the end-of-study visit, participants will be instructed to return all empty, partially used, and unused containers. Returned products will be reconciled against dispensing records, and adherence will be assessed by capsule count, expressed as the proportion of capsules taken relative to the expected intake over the intervention period. Any discrepancies (e.g., missed returns, lost containers) will be documented. Unused study products will not be re-dispensed and will be retained and/or disposed of in accordance with applicable institutional and local regulatory requirements.

### 2.6. Randomization, Allocation Concealment, and Blinding

Randomization will be conducted in a 1:1 ratio using a computer-generated allocation sequence prepared by independent personnel not involved in participant enrolment, clinical assessment, or outcome evaluation. The randomization list will be generated using an appropriate algorithm to ensure unpredictability of assignment and will be securely stored with controlled access to maintain allocation integrity throughout the study.

Allocation concealment will be ensured through the use of pre-packaged, sequentially assigned coded treatment kits/boxes, which will be indistinguishable in appearance and labelled with study-specific identification codes only. Study products will be dispensed according to the assigned kit code, thereby preventing foreknowledge of treatment allocation at the time of enrolment and throughout follow-up.

This will be a double-blind study. Participants, investigators, study staff involved in outcome assessment, and data analysts will remain blinded to group assignment until completion of all study procedures and database lock. Unblinding will be permissible only in exceptional circumstances where knowledge of the allocated intervention is deemed essential for the clinical management of a participant and to safeguard participant safety. Any emergency unblinding will be performed via a predefined procedure, fully documented (including rationale, date, and personnel involved), and promptly reported according to applicable regulatory and institutional requirements.

### 2.7. Schedule of Assessments

The timing of enrolment, allocation, intervention administration, and study assessments is summarized in Table 2, in accordance with SPIRIT (Standard Protocol Items: Recommendations for Interventional Trials). The study flow diagram is shown in Figure 1. All parameters collected during the study will be assessed using standardized methodologies [27,28].

### 2.8. Outcomes

#### 2.8.1. Primary Endpoint

The primary endpoint is the between-group comparison of the change in plasma 25(OH)D from baseline (day 0) to the end of the intervention (week 12/day 84). This endpoint was selected to capture the biological efficacy of the fish processing by-product-derived formulation in improving vitamin D status relative to the synthetic comparator under standardized dosing conditions.

#### 2.8.2. Secondary Endpoints

Secondary endpoints are intended to characterize biological correlations of vitamin D repletion, as well as the overall tolerability and safety profile of the interventions. Changes from baseline to week 12 will be assessed for key markers of mineral metabolism, including plasma calcium, phosphorus, and parathyroid hormone (PTH). In addition, given the clinical context and the interest in potential cardiometabolic correlates, changes will be evaluated in the fasting lipid profile—total cholesterol, LDL-C, HDL-C, and TG. These measures are included as exploratory cardiometabolic correlates and to exclude clinically relevant adverse shifts, acknowledging that evidence on vitamin D-related lipid effects is mixed across cholesterol fractions and more consistent for TG. Changes will also be assessed in anthropometric measures, including body weight, waist and hip circumferences, and BMI.

Tolerability and acceptability will be captured through structured participant assessment/interview as specified in the protocol, alongside systematic collection of adverse events throughout follow-up. Safety outcomes include the incidence of adverse events and serious adverse events, withdrawals due to adverse events, and clinically relevant changes in vital signs.

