#### 2.8.3. Exploratory Endpoints

To explore early response patterns, the trial will additionally examine the short-term kinetics of plasma 25(OH)D through intermediate sampling at 72 h, day 7, and day 28, thereby providing a descriptive time-course profile of vitamin D status changes under the two formulations.

All endpoints will be assessed according to the schedule reported in Table 2.

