### 2.10. Safety Monitoring and Adverse Events

Adverse events (AEs) will be collected from the time of informed consent until the end-of-study visit. AEs will be captured through spontaneous participant reporting as well as through structured assessment at each study contact, including targeted questioning and review of concomitant medications and clinically relevant findings. Any sleep-related complaints potentially occurring during supplementation (e.g., insomnia or changes in perceived sleep quality) will be recorded as part of the adverse event assessment. Each AE will be documented with onset and resolution dates, severity (e.g., mild/moderate/severe), outcome, and any action taken regarding the study intervention. All events will be evaluated for seriousness and for their potential relationship to the study product based on clinical judgement and temporal plausibility. Serious adverse events (SAEs) will be managed, documented, and reported in accordance with institutional procedures and applicable regulatory requirements, with timely communication to the appropriate oversight bodies when indicated. Participants may discontinue the intervention at any time without prejudice. Criteria for withdrawal include participant request, unacceptable intolerance, intercurrent conditions requiring discontinuation, protocol deviations that may compromise safety, or safety concerns at the investigator’s discretion. Where feasible, participants who discontinue the intervention will be encouraged to complete end-of-study assessments, and all AEs will be followed until resolution, stabilization, or a clinically acceptable outcome.

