## Figures and Tables

**Figure 1 jcm-15-01186-f001:**
[figure not shown]
Study flow diagram of the D-FISH trial. After screening and informed consent, eligible participants are randomized 1:1 to receive fish processing by-product-derived or synthetic vitamin D_3_ (600 IU/day) for 12 weeks (one capsule daily with the evening meal). Assessments are performed at day 0, day 3 (72 h), day 7, day 28, and day 84. Adverse events are collected throughout follow-up.

**Table 1 jcm-15-01186-t001:** Eligibility criteria.

Section	Criteria
Inclusion criteria	(1) Men or women aged 18–60 years (2) Plasma 25(OH)D between 20 and 40 ng/mL (3) Ability to understand study procedures and comply with trial requirements (4) Written informed consent provided prior to any study-related procedure
Exclusion criteria	(1) Current intake of vitamin D-containing supplements or medications (2) Osteopenia/osteoporosis, rheumatologic diseases, or history of non-traumatic fractures (3) Known hyperparathyroidism, hypercalcemia, or severe renal failure (eGFR < 30 mL/min/1.73 m^2^) (4) Known fish allergy/intolerance or allergy to fish-derived products (5) Preventive drug treatments (e.g., lipid-lowering or antihypertensive agents) not stable in type and dose for ≥3 months (6) Pregnancy or lactation (7) Any condition likely to compromise adherence to the protocol (including clinically relevant malabsorption syndromes)

25(OH)D, 25-hydroxyvitamin D; eGFR, estimated glomerular filtration rate.

**Table 2 jcm-15-01186-t002:** SPIRIT (Standard Protocol Items: Recommendations for Interventional Trials) schedule of enrolment, interventions, and assessments for the D-FISH trial.

Procedures/Assessments	Enrolment/ Baseline (Day 0)	72 h (±1 Day)	Day 7 (±1 Day)	Day 28 (±3 Days)	End of Study (Day 84 ± 5 Days)
Informed consent	X				
Eligibility assessment	X				
Randomization (1:1)	X				
Dispense study product	X				
Study product intake (daily, 600 IU/day)	X	X	X	X	X
Concomitant therapies review	X				X
Vital signs	X				X
Anthropometrics (weight, height, waist, hip; BMI)	X ^†^				X ^‡^
Adverse events assessment	X	X ^§^	X ^§^	X ^§^	X
Tolerability/acceptability interview					X
Pill count/accountability					X
Blood sampling: 25(OH)D	X	X	X	X	X
Blood sampling: calcium, phosphorus, PTH	X				X
Blood sampling: lipid profile (TC, LDL-C, HDL-C, TG)	X				X

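### The only scheduled tolerability/acceptability interview is at day 84, so participants who stop early for intolerance may be under-represented in it

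*Protocol article*

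**What the plan says.** Section 2.8.2 names the instrument: "Tolerability and acceptability will be captured through structured participant assessment/interview as specified in the protocol". The same sentence pairs it with a second source, "alongside systematic collection of adverse events throughout follow-up", and the section adds a countable outcome: "Safety outcomes include the incidence of adverse events and serious adverse events, withdrawals due to adverse events".

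Timing is fixed in the article. Section 2.8.3 states: "All endpoints will be assessed according to the schedule reported in Table 2". In Table 2 the row "Tolerability/acceptability interview" carries a single mark, in the end-of-study column (day 84 ± 5 days). The table has no column for early discontinuation.

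On stopping, Section 2.10 says: "Criteria for withdrawal include participant request, unacceptable intolerance, intercurrent conditions requiring discontinuation", followed by other reasons. For those who stop: "Where feasible, participants who discontinue the intervention will be encouraged to complete end-of-study assessments".

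Two places describe what happens at the intermediate contacts (72 h, day 7, day 28). Section 2.10 says AEs are captured by structured assessment at each study contact. The Table 2 footnote to the AE row says a brief AE/tolerability check is something the site may do, depending on its logistics.

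**The concern.** The interview measures how well the capsule was tolerated and accepted, and the plan expects some participants to leave for that very reason. Someone who stops at day 10 has no scheduled interview until about ten weeks later, and attendance then rests on encouragement. Whether the interview is missing can thus depend on the answer it would have given.

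Short-term tolerability is one of the trial's declared aims, in the abstract and in the conclusion. An interview held mainly with people who finished the course describes tolerability among finishers. The two capsules also differ in content (Sections 2.5.1 and 2.5.2): a microencapsulated sardine extract with several excipients against a medium-chain triglyceride vehicle. Unequal loss between arms is conceivable, though nothing in the document shows it.

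**Working it through.** **Inputs from the article.** 24 participants per group and an allowance of about 10% for drop-out and non-compliance exclusions (Section 2.11); interview at day 84 ± 5 only (Table 2). The article gives no expected intolerance rate and no expected interview completion rate, so both are assumed below.

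**The plan's own figure.** The article has no number for the interview. Its sample size, which supplies the denominator, can be reproduced for the primary endpoint: n per arm = 2 × SD² × (z₁₋α + z₁₋β)² / margin² = 2 × 5.5² × (1.645 + 1.282)² / 5² = 20.7, so 21. Then 21 / 0.9 = 23.3, so 24 per arm and 48 in all. This takes one-sided α = 0.05, which is inferred because the article states no α. Nothing below depends on it.

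**Scale of the allowance.** 10% of 24 is 2.4, so about two per arm. Three per arm would be 3/24 = 12.5%, above the allowance, which also has to cover every other reason for loss.

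**Effect on the interview rate.** Let I be the number truly intolerant in an arm of 24, and k the number of them who stop and are never interviewed. The true rate is I/24 and the interview shows (I − k)/(24 − k).

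| k missed | I = 4 (true 16.7%) | Understated by | I = 6 (true 25.0%) | Understated by |
|---|---|---|---|---|
| 0 | 4/24 = 16.7% | 0 | 6/24 = 25.0% | 0 |
| 1 | 3/23 = 13.0% | 3.6 points | 5/23 = 21.7% | 3.3 points |
| 2 | 2/22 = 9.1% | 7.6 points | 4/22 = 18.2% | 6.8 points |
| 3 (assumed extreme) | 1/21 = 4.8% | 11.9 points | 3/21 = 14.3% | 10.7 points |

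The understatement runs from zero to about 12 points and depends wholly on how many stoppers are missed.

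**Between arms.** With I = 4 in both arms and k = 2 in both, each shows 9.1% and the difference stays at zero. With k = 2 in one arm only, the rates are 9.1% and 16.7%, a spurious 7.6 points in favour of the arm that lost people. The document gives no basis for saying which arm that would be, or whether either would.

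**The safeguards side by side.** Section 2.10 describes structured AE assessment at every contact; the Table 2 footnote leaves the check at three of the five scheduled contacts to the site. A site following the footnote could reach day 84 without any structured tolerability question after day 0. The two statements need to be reconciled.

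**The case against.** The strongest reply is that tolerability does not rest on the interview alone. AEs are collected throughout, with severity, outcome and action taken, and withdrawals due to AEs are counted. An intolerance that ends treatment would normally appear there. Section 2.10 also encourages stoppers to complete the final assessments, which include the interview, so the loss may be nil. The article further refers interview details to a fuller protocol that is not shown, and Section 3 already limits the safety findings to short-term signals.

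Much of this stands, and it makes the point a modest one. Three things remain. The interview's timing is fixed in this article by Table 2 and Section 2.8.3, so it is not merely deferred. Section 2.10 lists participant request and intolerance as withdrawal reasons in their own right, so someone who stops because the capsule is unpleasant need not be recorded as an AE withdrawal. And no other scheduled source is named for acceptability.

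A reader might go further and infer that the tolerability outcome is biased toward a favourable result. The documents do not support that: the bias arises only if stoppers miss the interview, and its between-arm direction is open.

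A reader might also infer that an end-of-study blood sample taken on the day of stopping would enter the full analysis set as a day-84 value. That does not follow either. Section 2.8.1 fixes the endpoint at day 84, Table 2 defines end of study as day 84 ± 5, and Section 2.8.3 ties all endpoints to that table. That reading would also put the interview on the stopping day, which would remove the present concern.

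**Conclusion.** The point holds as a risk to one secondary outcome. The only scheduled interview falls at day 84 ± 5, early stoppers reach it by encouragement alone, and the intermediate check that could stand in for it is optional in one place and promised in another. Interview results, and acceptability most of all, may under-represent intolerant participants.

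The size cannot be stated from the documents. With 4 intolerant of 24 assumed, and losses near the plan's allowance (two per arm, all of them intolerant and none interviewed), the interview would show 9.1% instead of 16.7%. The 4.8% figure needs three such losses and is an assumed extreme. If every stopper attends, there is no effect. AE collection and AE withdrawals recover part of any loss. The primary endpoint, the sample size and the non-inferiority rule are unaffected.

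**What to change.** 1. In Table 2, add the tolerability/acceptability interview at the contact where a participant discontinues, by phone if needed. Keep the day 84 assessments as scheduled for these participants.
2. Reconcile the Table 2 footnote with Section 2.10, so that the brief AE/tolerability check is done at the existing 72 h, day 7 and day 28 contacts.
3. Report discontinuations for intolerance, by arm, beside the interview results in the safety set. In the example above, two interviewed as intolerant plus two who stopped for intolerance gives back 4/24 = 16.7%.

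The cost is an added Table 2 entry, a sentence in Section 2.10, and a few extra minutes at contacts that already take place. It needs no new visit and no further blood draw.

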#### 2.8.3. Exploratory Endpoints

To explore early response patterns, the trial will additionally examine the short-term kinetics of plasma 25(OH)D through intermediate sampling at 72 h, day 7, and day 28, thereby providing a descriptive time-course profile of vitamin D status changes under the two formulations.

All endpoints will be assessed according to the schedule reported in Table 2.

### 2.9. Adherence, Concomitant Treatments, and Protocol Deviations

Participants will be instructed to take one capsule once daily with the evening meal throughout the 12-week intervention period, in accordance with the assigned study regimen. At each contact, participants will be reminded to maintain consistent intake habits and to report any missed doses or interruptions. Adherence will be evaluated at the end-of-study visit primarily by capsule count and will be corroborated by a structured participant interview aimed at capturing dosing regularity, reasons for missed doses, and any difficulties in maintaining the prescribed schedule.

Concomitant treatments will be permitted provided they are clinically indicated and remain stable throughout the trial. Any changes in background therapy occurring during follow-up, including dose adjustments, temporary discontinuations, or initiation of new medications, will be systematically recorded. In order to minimize confounding and preserve interpretability of the intervention effect, the initiation of vitamin D-containing supplements or medications during the study period will not be allowed; participants will therefore be instructed to avoid any new over-the-counter preparations containing vitamin D.

Protocol deviations will be prospectively documented in a dedicated deviation log, including their nature, timing, and potential impact on study conduct and endpoints. Deviations will be reviewed prior to database lock by the study team in order to classify their relevance and define the per-protocol analysis set according to pre-specified criteria.

### 2.10. Safety Monitoring and Adverse Events

Adverse events (AEs) will be collected from the time of informed consent until the end-of-study visit. AEs will be captured through spontaneous participant reporting as well as through structured assessment at each study contact, including targeted questioning and review of concomitant medications and clinically relevant findings. Any sleep-related complaints potentially occurring during supplementation (e.g., insomnia or changes in perceived sleep quality) will be recorded as part of the adverse event assessment. Each AE will be documented with onset and resolution dates, severity (e.g., mild/moderate/severe), outcome, and any action taken regarding the study intervention. All events will be evaluated for seriousness and for their potential relationship to the study product based on clinical judgement and temporal plausibility. Serious adverse events (SAEs) will be managed, documented, and reported in accordance with institutional procedures and applicable regulatory requirements, with timely communication to the appropriate oversight bodies when indicated. Participants may discontinue the intervention at any time without prejudice. Criteria for withdrawal include participant request, unacceptable intolerance, intercurrent conditions requiring discontinuation, protocol deviations that may compromise safety, or safety concerns at the investigator’s discretion. Where feasible, participants who discontinue the intervention will be encouraged to complete end-of-study assessments, and all AEs will be followed until resolution, stabilization, or a clinically acceptable outcome.

### 2.11. Sample Size Determination

The planned sample size is 48 participants (24 per group). The calculation is based on a non-inferiority framework for the primary endpoint, assuming a standard deviation of 5.5 ng/mL for the change in 25(OH)D, a non-inferiority margin of 5 ng/mL, 90% power, and an allowance for approximately 10% drop-out and exclusions due to non-compliance. The non-inferiority margin (5 ng/mL, ~12.5 nmol/L) was prespecified to represent a conservative and clinically acceptable difference in biochemical response between formulations at nutritional doses while preserving feasibility for this proof-of-concept trial. Although no universally accepted minimal clinically important difference for 25(OH)D change exists, the margin was selected a priori to avoid differences likely to be regarded as meaningful in routine biochemical monitoring.

### 2.12. Statistical Analysis Plan

Analyses will be conducted in predefined analysis populations: a full analysis set (FAS; intention-to-treat principle), a per-protocol (PP) set excluding major protocol deviations, and a safety set including all participants who receive at least one dose of study treatment.

For the primary endpoint, non-inferiority of fish-derived vitamin D_3_ versus synthetic vitamin D_3_ will be concluded if the lower bound of the confidence interval for the between-group difference (fish-derived minus synthetic) in the change in 25(OH)D at week 12 is above −5 ng/mL. A repeated-measures ANCOVA model will be used, with treatment group and visit as factors and baseline 25(OH)D as a covariate. The primary analysis will be performed in the FAS and repeated in the PP set as a sensitivity analysis.

Secondary continuous outcomes will be analyzed using ANCOVA models with treatment group as factor and baseline value as covariate (or appropriate non-parametric alternatives if model assumptions are not met). Categorical outcomes (e.g., AE incidence) will be summarized as counts and percentages and compared using appropriate tests where relevant. As an exploratory sensitivity analysis, the month/season of blood sampling may be included as a covariate to assess the robustness of the primary comparison. No interim analysis is planned.

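### The primary model as listed names no treatment-by-visit term and no day-84 contrast, so it does not by itself yield the week-12 difference that the non-inferiority rule needs

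*Protocol article*

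**What the plan says.** Section 2.8.1 defines the primary endpoint as a between-group comparison of "the change in plasma 25(OH)D from baseline (day 0) to the end of the intervention (week 12/day 84". Section 2.12 bases the decision on the same time point: non-inferiority is concluded if the lower confidence limit for the "between-group difference (fish-derived minus synthetic) in the change in 25(OH)D at week 12 is above −5 ng/mL".

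The next sentence of 2.12 gives the model: "A repeated-measures ANCOVA model will be used, with treatment group and visit as factors and baseline 25(OH)D as a covariate". No interaction, contrast or set of visits is specified.

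Table 2 schedules 25(OH)D at day 0, 72 h, day 7, day 28 and day 84. Section 2.8.3 makes the three middle samples exploratory, describing "intermediate sampling at 72 h, day 7, and day 28, thereby providing a descriptive time-course profile". Section 2.11 sizes the trial by "assuming a standard deviation of 5.5 ng/mL for the change in 25(OH)D", with "a non-inferiority margin of 5 ng/mL, 90% power" and "an allowance for approximately 10% drop-out and exclusions due to non-compliance", giving 48 participants (24 per group).

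**The concern.** A repeated-measures model with a visit factor needs more than one post-baseline visit. If treatment and visit enter only as the listed terms, the model holds the treatment effect equal at all visits and estimates a single value. That value is a weighted mean of the visit-specific differences, whereas the rule asks for the difference at one visit.

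The gap matters because of its likely direction. Randomised arms have no expected difference at day 0, and a shortfall in one product would have to accumulate with daily capsules. Two of the four post-baseline samples fall in the first week. Averaging them in would pull a week-12 shortfall toward zero, which in a non-inferiority trial is the anti-conservative direction. The Discussion itself allows that the two formulations may follow different time courses, and that is what a treatment-by-visit term represents. The trial's only confirmatory claim rests on this model.

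**Working it through.** **1. What the sample size assumes.** Inputs from 2.11: SD 5.5, margin 5, power 90%, drop-out about 10%. The formula per arm is n = 2(z_alpha + z_beta)^2 SD^2 / margin^2.
- One-sided 0.05: 2 x (1.645 + 1.282)^2 x 30.25 / 25 = 20.7, so 21; 21/0.9 = 23.3, so 24 per arm and 48 in total. This matches the article.
- One-sided 0.025: 2 x (1.960 + 1.282)^2 x 30.25 / 25 = 25.4, so 26; 26/0.9 = 28.9, so 29 per arm and 58 in total. This does not match.

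The stated 48 is therefore reproduced by a comparison at a single time point, with no gain from averaging over visits. The article does not state the confidence level, so both 90% and 95% intervals are carried below.

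**2. What the listed terms estimate.** Assumption (not in the article): the between-arm difference grows as f(t) = 1 - exp(-ln2 x t/h), with half-time h. Ratios f(t)/f(84):

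| h (days) | 72 h | day 7 | day 28 | day 84 | mean | estimate when the true week-12 difference is -5 |
|---|---|---|---|---|---|---|
| 10 | 0.188 | 0.386 | 0.859 | 1 | 0.608 | -3.04 |
| 20 | 0.104 | 0.228 | 0.657 | 1 | 0.497 | -2.49 |
| 30 | 0.078 | 0.174 | 0.556 | 1 | 0.452 | -2.26 |

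**3. False non-inferiority at a true -5.** Further assumptions: SD 5.5 at every visit, common within-person correlation rho, 24 per arm, equal weight for each visit. The standard error of the averaged effect is SE = 5.5 x sqrt((1 + 3 rho)/4) x sqrt(2/24), which is 1.18, 1.33 and 1.46 for rho = 0.4, 0.6 and 0.8. P(declare non-inferiority) = Phi((5 + estimate)/SE - z).
- Lowest (h = 10, rho = 0.8): (5 - 3.04)/1.464 = 1.34. This gives Phi(1.34 - 1.645) = 38% with a 90% interval and Phi(1.34 - 1.96) = 27% with a 95% interval.
- Highest (h = 30, rho = 0.4): (5 - 2.26)/1.177 = 2.33. This gives Phi(2.33 - 1.645) = 75% and Phi(2.33 - 1.96) = 64%.

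**4. Check by simulation.** 22 per arm, 95% interval, 2,000 runs per scenario, correlation 0.4 or 0.7, build-up linear or exponential with half-times from 10 to 45 days.
- Averaged effect, SD 5.5 throughout: 26-69% false non-inferiority.
- Averaged effect, SD growing over the visits (2, 3, 4.5, 5.5): 48-95%.
- Day-84 ANCOVA on the same data: about 2-3%, against nominal 2.5%.
- Difference constant from 72 h onward: the averaged estimate stays at about -5 and the error at 2.1-2.5%, so there is no bias in that case.

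**The case against.** The strongest reply is that the article never says the model has main effects only. Naming two factors in a repeated-measures model does not exclude their interaction, and the preceding sentence ties the interval to week 12. On that reading the week-12 contrast was always intended, and its specification sits in a full protocol or analysis plan that is not shown. The article also does not say that all four post-baseline visits enter the primary model, and it gives no kinetics, early SDs or correlations.

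Most of this stands. A reader might infer that the plan fixes a main-effects model over all four visits, that the estimate is certainly biased, and that the type I error is uncontrolled. The text does not support that inference: the first two elements are read from silence, and the bias depends on a difference that grows over time.

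The reply does not remove the mismatch. The article chose to list the primary model's terms, and those terms, taken as written, give a different quantity from the one its rule uses. In the same section the secondary ANCOVA is described in the same style, and there the list is a complete model. An analyst could reasonably enter the primary terms as listed.

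**Conclusion.** The point holds as a mismatch between rule and model: the listed terms do not deliver the day-84 contrast required by 2.8.1 and 2.12. Whether this distorts the result depends on how the sentence is implemented and on the time course. With a day-84 contrast, the false non-inferiority rate is close to nominal. With the literal listed terms over four visits and a deficit that builds up, a true -5 ng/mL is estimated at about -3.0 to -2.3, and the rate is about 38-75% (90% interval) or 27-64% (95% interval). These figures illustrate one reading under assumed half-times, correlations and a constant SD; they do not predict this trial's error rate. They do show that the primary conclusion can turn on a choice the text leaves open, which is reason enough to settle it before unblinding.

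**What to change.** In 2.12, do one of the following:
- Add treatment-by-visit and baseline-by-visit terms to the repeated-measures model, and state that non-inferiority is judged on the day-84 treatment contrast from it.
- Make the primary model an ANCOVA of the day-84 change on treatment and baseline 25(OH)D, and keep the 72 h, day 7 and day 28 samples for the exploratory kinetics.

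The cost is about two lines of text. The standard error becomes that of the day-84 contrast: before baseline adjustment, 5.5 x sqrt(2/24) = 1.59, against 1.18 to 1.46 for the averaged effect. The sample size already assumes that precision, so this change needs no extra participants. If the interaction was always intended, the edit only records it.
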